## **1.0 BACKGROUND AND SIGNIFICANCE**

### **1.1 BACKGROUND**

Trigger finger (TF), or the stenosing tenosynovitis describes disproportionate size of a flexor tendon and tendon sheath at the first annular pulley (A1) at the metacarpophalangeal joint (MCPJ) (Lunsford et al. 2017). It is a common condition of the hand thought to be caused by inflammation or thickening of the tendon tissues that interferes with gliding of the tendon, which may in turn cause pain, clicking, catching and loss of motion (Makkouk et al. 2008). In the early stages, there may be local tenderness and swelling and with time a discrete nodule may form in the area of the A1 pulley (Gil et al. 2020). In severe cases, the affected finger can lock in flexion or extension and cause sharp pain when the finger is actively or passively unlocked. Although the cause of TF is unclear, there is a higher prevalence among people with metabolic diseases such as diabetes mellitus, hypothyroidism, mucopolysaccharidosis, and other inflammatory arthropathies (Gil et al. 2020). In adults the incidence of TF is 28:100,000 per year with a 2.6% lifetime incidence of TF in adults (Akhtar et al. 2005), and a higher prevalence in adult diabetics of between 5% and 20% (Kuczmarski et al. 2018). TF is reported to be more common in middle-aged individuals and women are six times more likely to develop TF than men (Akhtar et al. 2005).

TF can affect hand functions which include precision of work, speed of hand performance, gross power grip, 3-jaw chuck pinch, and manipulation, causing difficulties in performing daily activities (Langer et al. 2017; Lunsford et al. 2017). Poor hand function in people with TF has been reported to contribute significantly to disability (Langer et al. 2016). Financially, treatment of TF by steroid injection or surgery is expensive as pointed out by Zhuang et al. (2020) who compared costs for two different health insurance payers in the United States of America. The cost of a single steroid injection was between \$75.57 (commercial) and \$49.26 (Medicare) and the cost of surgery was between \$902 (commercial) and \$853 (Medicare), respectively. Given that the success rate of a single steroid injection for TF was reported to be about 50%, half of all patients will either have a second injection or will have surgery recommended (Zhuang et al. 2020).

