For the RME splint, a strip of thermoplastic will be woven around on the proximal phalanx of all four fingers with the MCPJ of the affected finger(s) positioned in approximately 20°-25° more extension than MCPJ of the adjacent fingers. For the RMF splint, the thermoplastic strip will be woven with the MCPJ of the affected finger(s) positioned in approximately 20°-25° more flexion than the MCPJ of the adjacent fingers. The angle of MCPJ will be increased if 20°-25° flexion/extension is not enough to reduce/stop pain or triggering. For MCPJ blocking splint, the thermoplastic material will be moulded to contour the palm over the MCPJ and formed into a circumferential "ring" around the proximal phalanx of the affected finger(s). After the splint was fabricated, the participants will have to wear the splint for 15 minutes to check if the splint has pressure points that can cause pain or any redness of the skin. If there are pain and redness, the splint will be readjusted to prevent these pressure points. For all splints, each participant will be asked to assess the comfort and satisfaction with the splint before leaving the clinic.

The RMG and MCPJBG participants will receive same education and conventional treatment. Each participant will be instructed to wear the splint full time (24-hours) every day and night for six weeks, with the exception that the splint can be removed for hygiene purposes including washing hands and showering. No gripping when out of splint. To track splint wearing adherence, each participant will be given a diary to record the hours the splint was worn in a 24-hour period. Participant will also be asked to record what task(s)he/she has

removed the splint. Each participant will be informed about the condition of TF including symptoms, cause, risk factor, and treatment. Participants will also be encouraged to modify activities that may provoke their TF symptoms while wearing the splint. Suggestions for activity modification include stopping or limiting activities that involve repetitive hand use and prolonged gripping. Participants will be asked to contact the researcher if there are any problems with the splint that affect wear or to replace the splint if participant has accidentally lost their splint. The researcher will arrange an appointment as soon as possible with them to address these problems and make note of this interruption in intervention.

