Each participant will be required to attend three sessions of therapy over the study period of six weeks. These sessions ideally will be the initial therapy session (Week-1), then three weeks later (Week-3), and six weeks after the initial session (Week-6). At Week-3, Therapist B will conduct the VAS assessment (comfort, and satisfaction) and provide the conventional therapy to each participant. Therapist B will perform a deep circular massage over A1 pulley for 5 minutes and each participant will be taught how to do the deep circular massage at home. The researcher will inspect each participant's splint and adjust it accordingly based on the participant's comments.

At Week-6, Therapist A will administer the post-intervention assessment for all participants. Table 1.0 outlines the procedure involved in RMG and MCPJBG. Figure 1.0 is the flowchart of the procedure.

Table 1.0 Procedure involved in Relative Motion Group and Metacarpophalangeal Joint Blocking Group.

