| Week 1 (Day 1)
Assessment 
 
Demographic questionnaire
 
Pre-intervention assessments               
 
DASH
 
COPM
 
VAS (Pain, Comfort, & Satisfaction)
 
Number of Triggering Events in Ten Active Fists
 
SST
 
 
 

Splint 
 
RME pencil test
 
RMF pencil test
 
Fabricate RME splint or RMF splint
 
MCPJ of the affected finger is approximately 20°-25° extension/flexion than the MCPJ of the adjacent fingers
 
Increase the angle if 20°-25° MCPJ extension/flexion of affected finger is not enough to reduce/stop the triggering/pain
 

Patient Education 
 
Splint wear full time for 6 weeks, only remove for hygiene purpose
 
No gripping when out of splint
 
Provide a diary to record everyday splint wear duration (hours)
 
Record what task the splint is removed for
 
About TF condition
 
 | Week 1 (Day 1)
Assessment 
 
Demographic questionnaire
 
Pre-intervention assessments               
 
DASH
 
COPM
 
VAS (Pain, Comfort, & Satisfaction)
 
Number of Triggering Events in Ten Active Fists
 
SST
 
 
 

Splint 
 
Fabricate MCPJ blocking splint
 
MCPJ positioned at 0°
 

Patient Education 
 
Splint wear full time for 6 weeks, only remove for hygiene purpose
 
No gripping when out of splint
 
Provide a diary to record everyday splint wear duration (hours)
 
Record what task the splint is removed for
 
About TF condition
 
Reduce or avoid activities such as repetitive hand use and prolonged grip or any action that causes pain/triggering
 
 |

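### Home massage over the A1 pulley is not reconciled with the hygiene-only splint-removal rule, and the tension falls mainly on the blocking arm, so equal co-treatment from Week 3 is not assured

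*Protocol*

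**What the plan says.** All of the following is in Protocol section 3.8, including Table 1.0, unless another section is named.

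- **Co-treatment.** The two arms are meant to be alike apart from the splint: "The RMG and MCPJBG participants will receive same education and conventional treatment".
- **Massage.** At the Week 3 visit a therapist treats the pulley in the clinic for five minutes. Teaching for self-treatment follows in both arms: "each participant will be taught how to do the deep circular massage at home". No frequency, duration or timing is given for the home massage.
- **Wear rule.** Wear is round the clock for six weeks. The text gives one exception: "the splint can be removed for hygiene purposes including washing hands and showering". Table 1.0 repeats this for each arm: "Splint wear full time for 6 weeks, only remove for hygiene purpose".
- **Splints.** For the blocking splint, "the thermoplastic material will be moulded to contour the palm over the MCPJ", with a ring around the proximal phalanx. For the RM extension splint, "a strip of thermoplastic will be woven around on the proximal phalanx of all four fingers"; the RM flexion splint uses the same kind of strip.
- **Site.** Section 1.1 places the A1 pulley at the MCPJ.
- **Records.** The diary takes hours worn per day and the tasks for which the splint was removed. No entry for home massage is described. The Week 3 row of Table 1.0 lists the clinic massage but not the home massage.

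**The concern.** Two instructions given to the same participant do not sit together, and the strain between them depends on the allocated device. Someone in the blocking arm who wants to massage the pulley has rigid thermoplastic over it and permission to remove it only for hygiene. Someone in the RM arm appears to face no such obstacle.

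Home massage is aimed at the diseased structure and runs up to the Week 6 visit, when severity stage, pain, triggering, DASH and COPM are measured again. If uptake differs by arm, or if blocking-arm participants give up wear time to do it, that difference becomes part of the Week 6 comparison. Randomisation does not protect against it, because it arises after allocation and through the allocated splint.

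**Working it through.** No arithmetic in the protocol bears on this point, so the check is a comparison of the instructions.

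**Step 1. Is the massage site under the splint?**
- Blocking arm: yes. Section 1.1 puts the pulley at the MCPJ, and section 3.8 puts the splint over the palm at the MCPJ. Section 1.1 also describes a published minimal-profile blocking splint, secured by a ring on the proximal phalanx, as covering the palmar side of that joint.
- RM arm: apparently not. The strip is at the proximal phalanges and no palmar cover of the MCPJ is described. The protocol does not say that the site stays free, so this is an inference.

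**Step 2. What can each arm do within the written rules?**

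| Option for home massage | RM arm | Blocking arm |
|---|---|---|
| With the splint on | Apparently possible | Site covered |
| During a hygiene break | Allowed | Allowed |
| Splint removed for massage | Outside the removal rule | Outside the removal rule |
| Massage skipped | Co-treatment not received | Co-treatment not received |

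Only the first row differs by arm. It is also the only option that needs no removal at all.

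**Step 3. What would the diary show?**

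| What happened | Diary entry |
|---|---|
| Massage with the splint on | None |
| Massage during a hygiene break | At most a hygiene removal |
| Splint removed for massage | Fewer hours worn, and massage as the task if the participant writes it |
| Massage skipped | None |

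The first and last rows look identical, and the second looks like ordinary hygiene. Only the third can be recognised. Massage received therefore cannot be compared between arms from the diary as described.

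**Step 4. How long does it last?** Massage is taught at Week 3 and outcomes are taken at Week 6: 6 − 3 = 3 weeks, or 3/6 = half of the treatment period.

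**Step 5. Can a bias be calculated?** In simple form, the part of a Week 6 difference due to massage is

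m × (p_RM − p_block),

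where m is the effect of home massage on the outcome and p is the proportion of each arm doing it. The protocol gives neither m nor either p. The product is zero if m = 0 or if uptake is equal, and it changes sign with the sign of the uptake difference. Lost wear time in the blocking arm would add a second term, which is also unknown. No figure can be derived.

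**The case against.** The strongest reply is that the instructions can be followed together. Hygiene breaks recur, since hand washing and showering are named, and no home dose is set, so massage in those breaks violates nothing written. This stands. A reader might infer that home massage can be done as instructed only in the RM arm, or that a blocking-splint participant must either skip it or break the wear rule. The documents do not support that.

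Three further objections have weight:

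- **Provision is equal.** Both arms get the same clinic massage from the same therapist and the same teaching. If a splint makes self-massage awkward, that is arguably part of its effect in daily use. This is fair as a reading of a comparison of splints as prescribed. It still leaves unknown how much of any difference came through massage, and section 3.8 presents the co-treatment as common to both arms.
- **The diary is not blind.** A removal made specifically for massage is a task that it asks for. This stands, and it narrows the gap to massage done with the splint on or in a hygiene break.
- **Table 1.0 is described as an outline.** Leaving out home massage is an omission, not a contradiction of the text.

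What the reply does not remove is that no sentence links the massage instruction to the removal rule, and that the resulting constraint appears to fall mainly on one arm.

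**Conclusion.** The point holds in limited form. Home massage and hygiene-only removal are not reconciled, and the tension lies mainly with the blocking arm. Equal co-treatment between Week 3 and Week 6 is not assured, and much of what happens would go unrecorded.

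The conclusion rests on the splint and pulley positions given in the protocol and on one inference, that the RM strip leaves the site reachable.

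A reader might go on to infer a bias in pain favouring the RM splint and express it as a share of the 12 mm minimal important difference. The protocol does not support this: any such figure would multiply an assumed massage effect by an assumed uptake gap. The bias could favour either arm and may be near zero.

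The matter is worth correcting because it concerns treatment delivery and data capture. A separate analysis plan cannot recover massage data that were never collected.

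**What to change.** 1. Reconcile the wear rule, the Week 3 home-massage teaching and Table 1.0 in section 3.8, so that one instruction on home massage and splint removal can be followed alike in both arms. Which rule applies is for the investigators to decide.
2. Show that instruction in Table 1.0 for both arms.
3. From Week 3, add a home-massage line to the existing diary in both arms: done or not, minutes, splint on or off.
4. Report this by arm beside the wear hours.

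The cost is a wording change in one section and its table, one diary line, and slightly more diary burden for participants. Sample size, visits and outcome measures are unaffected.

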### 3.9 Statistical Analysis Plan

Descriptive statistics will be used to summarize the Demographic data including age, gender, occupation, hand dominance, digit involved, associated medical conditions, and duration of triggering. Data will be analysed and described in total numbers, mean, and the pattern of data. Descriptive statistics will also be used to demonstrate the assessment outcomes including DASH, COPM, VAS (pain, comfort, and satisfaction), Number of Triggering in Ten Active Fists, and SST. An independent sample *t*-test, set at the significant level of 0.05 will be used to compare the baseline data between RMG and MCPJBG. A Two Way Mixed-ANOVA, set at the significant level of 0.05 will be used to compare the assessment outcomes, including DASH, COPM, VAS (pain, comfort, and satisfaction), Number of Triggering in Ten Active Fists, and SST between the RMG and MCPJBG. The interaction effect between these different variables will be analysed too. The results will show the percentage of variance in each effect regardless of size (Hypotheses 1 – 7).

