| Specific Objectives      | 
 
1) To compare the effectiveness of RM splint and MCPJ blocking splint on TF severity after six weeks of TF management.
 
2) To compare the effectiveness of RM splint and MCPJ blocking splint on pain after six weeks of TF management.
 
3) To compare the effectiveness of RM splint and MCPJ blocking splint on finger triggering after six weeks of TF management.
 
4) To compare the effectiveness of RM splint and MCPJ blocking splint on hand function after six weeks of TF management.
 
5) To compare the effectiveness of RM splint and MCPJ blocking splint on occupational performance after six weeks of TF management.
 
6) To compare the effectiveness of RM splint and MCPJ blocking splint on comfort after six weeks of TF management.
 
7) To compare the effectiveness of RM splint and MCPJ blocking splint on satisfaction after six weeks of TF management.
 
 |
| Study endpoints/outcomes | 
 
1) There is a difference in terms of severity staging of TF.
 
2) There is a difference in terms of pain.
 
3) There is a difference in terms of finger triggering.
 
4) There is a difference in terms of hand function.
 
5) There is a difference in terms of occupational performance.
 
6) There is a difference in terms of comfort.
 
7) There is a difference in terms of satisfaction.
 
                                                                                                                                                                                                                                                                                                                                                                                                                                                                                         |

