## **2.1 HYPOTHESES**

Hypothesis 1: There is a difference in terms of severity staging as measured by Stages of Stenosing Tenosynovitis (SST) between patients diagnosed with TF involving the A1 pulley who are prescribed a RM splint for six weeks and those prescribed a MCPJ blocking splint under the same conditions.

Hypothesis 2: There is a difference in terms of pain as measured by Visual Analog Scale (VAS) between patients diagnosed with TF involving the A1 pulley who are prescribed a RM splint for six weeks and those prescribed a MCPJ blocking splint under the same conditions.

Hypothesis 3: There is a difference in terms of finger triggering as measured by number of triggering events in ten active fists between patients diagnosed with TF involving the A1 pulley who are prescribed a RM splint for six weeks and those prescribed a MCPJ blocking splint under the same conditions.

Hypothesis 4: There is a difference in terms of hand function as measured by Disabilities of the Arm, Shoulder and Hand (DASH) Outcome Measure between patients diagnosed with TF involving the A1 pulley who are prescribed a RM splint for six weeks and those prescribed a MCPJ blocking splint under the same conditions.

Hypothesis 5: There is a difference in terms of occupational performance as measured by Canadian Occupational Performance Measure (COPM) between patients diagnosed with TF involving the A1 pulley who are prescribed a RM splint for six weeks and those prescribed a MCPJ blocking splint under the same conditions.

Hypothesis 6: There is a difference in terms of comfort as measured by Visual Analog Scale (VAS) between patients diagnosed with TF involving the A1 pulley who are prescribed a RM splint for six weeks and those prescribed a MCPJ blocking splint under the same conditions.

Hypothesis 7: There is a difference in terms of satisfaction as measured by Visual Analog Scale (VAS) between patients diagnosed with TF involving the A1 pulley who are prescribed a RM splint for six weeks and those prescribed a MCPJ blocking splint under the same conditions.

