## f. Canadian Occupational Performance Measure (COPM)

The Canadian Occupational Performance Measure (COPM) will be used to measure the participant's occupational performance. COPM, developed by the Canadian Association of Occupational Therapist, in collaboration with Health and Welfare Canada (Law et al. 1990), is a widely known interview-based assessment tool for measuring occupational performance. COPM uses a client-centered approach and requires the patient to report the types of activities that he/she is unable to accomplish and later, prioritize the meaningfulness and importance of the selected activities. During the interview, the patient must report and rate the satisfaction and the performance of the activities in three occupational therapy areas, i.e., self-care, productivity, and leisure. The importance, satisfaction, and performance of an activity are rated using a 10-point rating scale. A benefit of the COPM is that self-perceived changes in occupational performance problems can be assessed over time (Law et al. 1990). Berardi et al. (2019) found that COPM has good construct validity (Cronbach's  $\alpha=0.89$ ) and excellent test-retest reliability for the performance subtest (ICC=0.99) and the satisfaction subtest (ICC = 0.98). The minimal clinically important difference of the COPM is 3.0 points and 3.2 points for performance subtest and satisfaction subtest, respectively (Tuntland et al.2016).

[figure not shown]

[figure not shown]

Figure 1.0 CONSORT flow chart. This figure shows the flow of patients through the trial according to the criteria recommended in the CONSORT Guidelines.

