**VISUAL ANALOG SCALE (WEEK-1 / WEEK-6)**

**PAIN**

How much pain do you have when you are at rest?  
(Berapa banyak kesakitan yang adas emasa anda sedang rehat?)

[figure not shown]

How much pain do you have when you are performing activities?  
(Berapa banyak kesakitan yang ada semasa anda melakukan aktiviti?)

[figure not shown]

Notes (Catatan): .....

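### Seven equal-ranked hypotheses are each tested at 0.05 with no primary outcome, and the score and ANOVA effect that decide each hypothesis are left open

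*Protocol*

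**What the plan says.** - **Ranking.** The Research Synopsis lists seven endpoints, starting with "There is a difference in terms of severity staging of TF". Sections 2.1 and 2.2.2 repeat them as seven hypotheses and seven specific objectives: severity stage, pain, triggering, DASH, COPM, comfort and satisfaction. None is called primary or secondary.
- **Test level.** Section 3.9: "A Two Way Mixed-ANOVA, set at the significant level of 0.05 will be used to compare the assessment outcomes". It links the analysis to all seven hypotheses ("The results will show the percentage of variance in each effect regardless of size (Hypotheses 1 – 7") and states no adjustment and no order of testing.
- **Effects tested.** Section 3.9 compares the groups and adds: "The interaction effect between these different variables will be analysed too".
- **Scores.** The pain form has two items, "How much pain do you have when you are at rest" and "How much pain do you have when you are performing activities". The comfort and satisfaction forms also have a rest item and an activity item each. Section 3.1.1 f gives COPM separate important differences of "3.0 points and 3.2 points for performance subtest and satisfaction subtest, respectively".
- **Sample size.** Section 3.6 uses a pain score from one prior trial (4.65, SD 2.39, before treatment; 3.40, SD 2.44, after), 5% significance and 80% power. It arrives at 32 participants, or 36 with 10% dropout.

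**The concern.** The trial is sized for one test at 5%, but the analysis makes at least seven claims of equal standing, each at 5%. With no primary outcome, the protocol does not fix which result answers the general objective of comparing the two splints. A single significant result among many could then be given prominence, and the probability that at least one appears by chance exceeds 5%.

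Two further gaps make the number of tests indefinite. Four hypotheses (pain, COPM, comfort, satisfaction) each have two possible scores. Each mixed ANOVA also gives a group p-value and an interaction p-value, and the protocol does not say which one decides. Even pain, which drives the sample size, is not pinned to the rest item or the activity item. Section 3.8 says that participants and assessing therapists are unblinded, and most outcomes are self-reported, so these choices should be settled in advance.

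**Working it through.** **1. The plan's own figure.** From section 3.6, d = (4.65 − 3.40) / √[(2.39² + 2.44²)/2] = 0.518 and f = d/2 = 0.259, which the plan rounds to 0.26. For a two-group, two-time-point mixed ANOVA, take the interaction test with λ = f²·N·m/(1 − ρ), m = 2 and an assumed repeated-measures correlation ρ = 0.5. Then N = 32 gives power 0.812 and N = 30 gives 0.785. So 32 reproduces, and 32/0.9 = 35.6 rounds up to 36. The stated size therefore fits one interaction test at 0.05. The effect size is taken as given here.

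**2. Number of scores.** Severity stage 1 + pain 2 + triggering 1 + DASH 1 + COPM 2 + comfort 2 + satisfaction 2 = 11, for 7 hypotheses.

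**3. Independent tests.** P(at least one false positive) = 1 − 0.95^k.
- k = 7: 1 − 0.698 = 0.302
- k = 11: 1 − 0.569 = 0.431

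**4. Correlated tests.** The protocol gives no correlations, so these are assumed. Results are from equicorrelated normal test statistics, two-sided 0.05, 400,000 draws.

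| Assumed correlation | 7 tests | 11 tests |
|---|---|---|
| 0.3 | 27.1% | 37.6% |
| 0.5 | 23.0% | 30.4% |
| 0.7 | 17.8% | 22.3% |
| 0.8 | 14.8% | 18.0% |

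With a correlation of 0.7-0.8 within paired scores and 0.3-0.5 elsewhere, eleven tests give 29-35%.

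**5. Two effects per ANOVA.** If a significant group effect or a significant interaction could each be read as a splint difference, the count doubles. Under independence, 14 tests give 1 − 0.95^14 = 51% and 22 tests give 1 − 0.95^22 = 68%.

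**6. Which effect decides.** With N = 32, f = 0.26 and ρ = 0.5, power is 0.81 for the interaction. For the group main effect, where λ = f²·N·m/(1 + (m − 1)ρ), it is 0.38. The two tests are not interchangeable.

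**The case against.** **Correlation.** A reader might infer a flat 30-43% risk. That range holds only for independent tests, which is implausible here. The severity stages grade triggering and locking, the ten-fist count scores persistent locking as 10, DASH contains symptom items, and comfort and satisfaction concern the same splint at the same visits. This objection stands: 30% and 43% are upper figures for their test counts, and the assumed-correlation ranges belong beside them.

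**Eleven tests.** A reader might also infer that eleven scores will each be tested at 0.05. The protocol does not say so. Section 2.1 names one instrument per hypothesis, and paired items could be averaged or one could be chosen. This too stands. The supportable complaint is that the score is undefined, and the eleven-test figures are conditional.

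**Decision rule.** Nothing in the protocol says that one significant result establishes overall superiority. Seven separately reported hypotheses each keep their nominal 5%, and the protocol does not claim family-wise control. So it would be wrong to say that the protocol breaks a stated 5% family-wise level. But the general objective is one comparison of the two splints across all domains, and no outcome is designated to answer it.

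**A separate SAP.** Item scoring and multiplicity rules are often placed there, and one may exist. The ranking of objectives is a protocol matter, however, and this protocol sets seven equal hypotheses at 0.05 in a section that is itself titled as the statistical analysis plan.

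**Conclusion.** The point holds in a conditional form. The protocol names no primary outcome and tests seven equal hypotheses at 0.05, although it was sized on one pain score. With no true difference and one test per hypothesis, the chance of some false splint difference is 30% under independence and about 15-27% over assumed correlations of 0.3-0.8. If all eleven scores were tested separately, which the protocol neither states nor rules out, it would be 43%, or about 18-38% over the same correlations. Reading both ANOVA effects would raise these figures. All of them exceed 5%, but they describe the family of tests; each single test keeps its nominal level. That the ranking, the deciding score and the deciding effect are left open rests on the text alone and needs no assumption about correlation.

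**What to change.** Before outcome data are analysed, amend the synopsis and sections 2.1, 2.2 and 3.9 as follows.

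1. Name pain as the single primary outcome, in keeping with section 3.6, and specify one VAS item. Activity pain is a reasonable choice, but section 3.6 refers only to a pain score and does not dictate it.
2. Test it once at 0.05 with one stated treatment-effect test: the group-by-time interaction or, equivalently for pain's two time points, a between-group comparison of change from baseline to Week 6.
3. Make the other six objectives secondary, each with one named score. Report them with 95% confidence intervals and label them supportive or exploratory. A formal adjustment among them is optional and is not needed for this fix.

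**Cost.** Wording only, and less confirmatory weight for the secondary outcomes. The stated 32 evaluable does not change, because the primary test stays at 0.05. Keeping all seven hypotheses confirmatory would cost far more. With Bonferroni, 0.05/7 = 0.00714 per test, and power at 32 falls from 0.81 to 0.53 on the model above. Holding 80% would need about 50 evaluable, and 50/0.9 = 55.6, or 56 enrolled.
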